##### Inclusion criteria

2.2.2.1.

(1) Age 60 years and over; (2) score greater than 8 on the Montgomery and Åsberg Depression Rating Scale (MADRS) (which corresponds to mild depression, optimal cut-off) (Zimmerman et al., 2004); (3) ability to give informed consent; (4) sufficient command of the Portuguese language; and (5) willingness to participate in the intervention over the period of the study. The diagnosis of depression will be identified by a trained professional, using the DSM-5 as a reference (American Psychiatric Association, 2014).

##### Exclusion criteria

2.2.2.2.

(1) Lifetime psychotic symptoms (i.e., delusions, hallucinations); (2) current or a history of mania; (3) acute suicidality; and (4) dementia or other neurological disorder which could be related to the onset of depressive symptoms (e.g., Parkinson’s disease, stroke, multiple sclerosis); (5) current substance dependence (substance abuse will be tolerated); (6) not having attended a similar training in the last 3 months; (7) patients with the MMSE score below 24 points will not be included.

Participants will be informed about the study and conditions of participation individually and written informed consent will be obtained from each participant. Participants will be asked if they have a guardian for medical decision-making. In this case, if the potential participant generally meets the criteria for inclusion, a permission to participate will be obtained from the guardian.

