#### Sample size calculation

2.2.4.

In RCTs to calculate the sample size, four factors are required: significance level, power analysis, difference between groups, and standard deviation (SD; Charles et al., 2009). As there is only one RCT in Germany that applied the MCT-Silver, we chose to conduct a pilot study, and the sample size calculation for the RCT is calculated *a posteriori*. For the pilot study, we will include 32 participants, as 15–20 participants are needed to ensure the scientific validity of the results of a pilot study (Hertzog, 2008). The results of the pilot study will provide information on the above four factors as they are necessary for the calculation of the sample size.

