## Discussion

3.

MCT-Silver is a low intensity, CBT-based group intervention, which appears to have great potential in reducing depressive symptoms but further studies are needed to better validate its efficacy as the pilot study was limited due to lack of a control group (Schneider et al., 2018) as well as the lack of follow-up assessments. Only one RCT on MCT-Silver has been conducted (in Germany) (Schneider et al., under review).^3^ The efficacy of MCT-Silver for older adults with depression has not yet been studied in the Portuguese population and, therefore, the development of the present trial is essential.

Portugal is one of the countries of the Organization for Economic Co-operation and Development (OECD) with the highest consumption of antidepressants (OECD, 2019) and, despite international guidelines recommending complementary treatment with non-pharmacological interventions (American Psychological Association, 2019), in Portugal this practice is not common. Most people with depression are only treated with medications.

It is expected that the results of this trial will provide support for the efficacy of the Portuguese version of MCT-Silver on the reduction of depressive symptoms. Moreover, it is anticipated that participants in the MCT-Silver group will demonstrate greater reductions in metacognitive beliefs, dysfunctional attitudes, ruminative responses and (negative) attitudes towards aging, as well as greater improvements in quality of life and self-esteem compared to a TAU group. The results of this trial are expected to allow future implementation of MCT-Silver by mental health and psychiatry professionals in various contexts. The MCT-Silver programme aims to contribute to the psychosocial rehabilitation of older adults with depression. The trial illustrated in this protocol intends to assess the efficacy of MCT-Silver in the Portuguese population.

Since people with depression often have cognitive deficits (Muhammad and Meher, 2021), patients with significantly impaired cognitive abilities may have difficulty understanding MCT-Silver exercises. To overcome this limitation, we will apply the MMSE to screen for cognitive deficits. Other limitations may be transportation difficulties getting to sessions regularly, as well as health problems, which may limit participation in the study or the changes in medication during the course of the study.

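### Exclusion item 6 is worded in the wrong direction: read literally it bars people without recent similar training, and nothing else in the article corrects it

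*Protocol article*

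**What the plan says.** Section 2.2.2.2 of the protocol article, headed "Exclusion criteria", has seven items. The sixth is "6) not having attended a similar training in the last 3 months". The first, "1) Lifetime psychotic symptoms (i.e., delusions, hallucinations", shows how the list works: it names a condition, and a person who has it is kept out. Items 2 to 5 follow the same pattern (mania, acute suicidality, dementia or another relevant neurological disorder, substance dependence). The seventh is a full statement, "patients with the MMSE score below 24 points will not be included", and so gives its own direction.

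The inclusion list (section 2.2.2.1) has five items: age, MADRS score, capacity to consent, command of Portuguese, and "5) willingness to participate in the intervention over the period of the study". None concerns earlier training.

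**The concern.** Item 6 reads like an inclusion condition that was placed in the exclusion list with its negation left in. As printed, the rule selects the opposite of the group one would expect in a trial of a training programme.

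Eligibility criteria determine who is randomised and to whom the result applies. If the sentence were copied into a screening form, staff could follow it and turn away candidates without recent training, or read it in reverse and depart from the protocol as written. Recruitment runs through several hospital mental health services and through the media (section 2.2.3), so the two readings could coexist. Under the literal reading, participants in both arms would also bring recent exposure to a similar programme, which could leave less room for a difference between MCT-Silver and TAU. These consequences are conditional: they follow only if someone applies the text as it stands.

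**Working it through.** No arithmetic applies, and the plan has no figure to reproduce. The check is a logical reading of the item, followed by a search of the article for text that would change that reading.

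**Step 1: the literal rule.** Let A stand for 'attended a similar training in the last 3 months'.

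| Version | Rule | Person with A | Person without A |
|---|---|---|---|
| As printed | exclude if not A | passes item 6 | excluded |
| 'not' deleted, item stays in exclusion list | exclude if A | excluded | passes item 6 |
| Sentence moved unchanged to inclusion list | include only if not A | not eligible | passes item 6 |

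The printed rule confines the eligible set to A. Either repair confines it to the complement of A, so the two repairs are equivalent and both reverse the printed text.

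**Step 2: could the list be meant the other way?** Items 1 to 5 each exclude when the named condition is present. Item 7 contains a negation, but its negation states the consequence (the person is not included) and not the condition. Item 6 has no such wording, so it takes the direction of the heading and of items 1 to 5.

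**Step 3: is it corrected elsewhere?**
- Inclusion criteria (2.2.2.1): nothing on prior training.
- Randomization and blinding (2.2.3): covers recruitment and the monitoring of other interventions during the study. It does not restate the rule.
- Treatment as usual (2.2.5.1): covers concurrent care. It does not restate the rule.
- Data collection (2.2.6, Table 4): records medication, admissions, day-hospital use and follow-up programmes. It does not restate the rule.
- Data analysis (2.2.9): names previous or current treatment as a moderator, which does not settle who is eligible.

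**Step 4: does the literal rule fit the article's own account?** The Discussion says "The efficacy of MCT-Silver for older adults with depression has not yet been studied in the Portuguese population". On treatment that complements medication, it says "in Portugal this practice is not common", and adds that most people with depression receive medication only. A rule that admitted only people with a similar training in the preceding 3 months would draw on a group that the article itself presents as small. The Introduction likewise describes the programme as not yet validated for the Portuguese population. None of these sentences says outright that participants must be without recent training, but together they make the literal rule implausible as an intention.

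**The case against.** The strongest reply is that the intended meaning is hard to miss. Given what the Introduction and Discussion say about Portugal, a site that followed the text literally would find few people to recruit and would notice at once. The list is loosely drafted anyway, as item 7 shows. The error does not touch the randomisation method, the analysis or the sample size. The article is also a condensed account, and the operative screening wording is not shown.

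Much of this stands, and it limits the severity. It does not make the text right. A rule that must be read as its opposite is misstated, and it is stated in this article, not left to another document.

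A reader might go further and infer that the enrolled sample will consist entirely of recently trained people, that sites will screen differently, or that the treatment contrast will be diluted. The article does not support these as findings. Each requires literal application, which no section shows, and no data on carry-over are given. Nor can the screening form or registry entry be called wrong, since neither is available.

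One further caution concerns the repair. The article does not define what counts as similar training, and TAU may include psychoeducational and therapeutic groups (2.2.5.1). Once the direction is corrected, a broad reading of 'similar' could exclude patients because of their ordinary care. The full protocol may define the term, so this is a limit on the repair and not a separate fault.

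**Conclusion.** The item is wrong as written. Under its heading, item 6 excludes people without recent similar training and passes only those with it, and nothing else in the article reverses that. The contradiction between wording and heading is certain from the text. That the sponsor meant the opposite is an inference, well supported by the article's description of Portugal. It is best classed as a drafting inconsistency in an eligibility rule and not as a deliberate design choice.

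Severity is moderate: the rule is operative, but its intended sense is fairly evident. No effect on the trial can be put in numbers. Uneven screening and carry-over are possible consequences of literal application and have not been shown to occur.

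**What to change.** Reconcile item 6 with its heading before enrolment. Either delete 'not' and leave the item in section 2.2.2.2, or move the sentence unchanged to section 2.2.2.1. Both give the same eligible population. Check whether the screening form and the registry entry carry the same wording, and correct them only if they do. When making the change, confirm that the full protocol says which programmes count as similar, so that ordinary TAU groups are not caught unintentionally.

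The cost is about one word, plus notice to the ethics committees if the same text stands in the approved protocol. The Introduction describes the pilot as still in preparation, so at the time of writing the correction could precede enrolment. If recruitment has since begun, the sponsor should also state which reading was applied at screening.

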**Discussion:**

MCT-Silver is an innovative intervention, which aims to reduce dysfunctional thoughts as well as depression-related behaviors and coping strategies through the metacognitive perspective. Until now, the training has only been tested in Germany. It is expected that after 8 weeks of treatment and 3 months later, the experimental group will demonstrate significant reductions in depressive symptoms, metacognitive beliefs, dysfunctional attitudes and ruminative responses compared to the TAU group. Moreover, quality of life, self-esteem, and attitudes towards aging will be significantly improved in MCT-Silver compared to the TAU group.

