Metacognitive training for older adults with depression (MCT-Silver; Schneider et al., 2018; Bücker, 2019), is a cognitive-behavioral (CBT)-based group intervention, specifically designed for adults ages 60 years and older (all materials are available for free^1^). MCT-Silver aims to reduce the treatment gap by improving access to mental health care for the estimated 73% of older adults with depression who go untreated (Horackova et al., 2019). MCT-Silver is based on metacognitive training for psychosis (MCT; Moritz and Woodward, 2007) and metacognitive training for depression (D-MCT; Jelinek et al., 2015). Randomized controlled trials on D-MCT provide evidence for its efficacy on depressive symptoms (Jelinek et al., 2016), as well as metacognitive and negative cognitive beliefs (Hauschildt et al., 2022; Özgüç and Tanriverdi, 2022) at short- and intermediate follow-up intervals. Long-term efficacy of D-MCT remains equivocal (Jelinek et al., 2019). A pilot study examined the feasibility, acceptance, and effects of D-MCT as an add-on intervention in a group of older adults with depression who were completing an intensive inpatient treatment program (55+ years; *N* = 116). Per protocol analyses (*n* = 55) yielded a significant decrease in depressive symptoms (*d* = 1.06) and cognitive biases (*d* = 0.33). These results support the feasibility and acceptance of D-MCT among older adults with depression. A recently completed RCT in Germany, which compared MCT-Silver to an active control group (cognitive remediation; (Schneider et al., 2018)) yielded large and significant reductions on the primary outcome (Hamilton Depression Rating Scale) from baseline to post and 3-month follow-up (*d_MCT-Silver_* = 1.25 – 1.42; *d*_CR_ = 1.05 – 1.12). Group differences; however, did not reach significance (η_p_^2^ = 0.001 – 0.002). MCT-Silver yielded significant moderate to large effects compared to CR immediately following the intervention and after 3 months for self-reported depression (BDI-II: η_p_^2^ = 0.075 – 0.135) and rumination (RRS: η_p_^2^ = 0.087 – 0.127). A significant moderate effect was found for positive metacognitive beliefs (MCQ-PB) at post-assessment (η_p_^2^ = 0.067), but group differences did not reach significance at follow-up (η_p_^2^ = 0.027). Small reductions in negative cognitive beliefs (Dysfunctional Attitudes Scale-18B) at post- and at 3-month follow-up (*d_MCT-Silver_* = 0.24 – 0.30) were found for the MCT-Silver group, whereas negative cognitive beliefs were unchanged in the CR group (*d_CR_* = –0.06 – 0.06).

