### Aim

2.1.

The aim of this study is to evaluate the efficacy of MCT-Silver and its effects on depressive symptoms, dysfunctional beliefs, metacognitive beliefs, quality of life, ruminative responses, self-esteem and attitudes towards aging. The hypotheses that we want toexamine in this trial are the following:

Primary outcome: There will be a greater reduction in self-reported depression (as measured by the Beck Depression Inventory-II) for MCT-Silver vs. TAU (pre-post; pre-follow-up).Secondary outcomes: There will be a greater reduction in clinician-rated depression (MADRS), metacognitive beliefs (Metacognitions Questionnaire-30), self-reported depression (PHQ-9), dysfunctional beliefs (DAS-18B), ruminative responses (RRS), self-esteem (Self-Esteem Questionnaire), quality of life (WHO QOL-Bref??), and attitudes to aging (Attitudes to Aging Questionnaire) for MCT-Silver vs. TAU (pre-post; pre-follow-up).Tertiary outcome: Participants will rate the intervention positively on a satisfaction questionnaire administered after the 8-week intervention period.

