#### Study design

2.2.1.

This study represents an observer-blind, parallel-groups randomized controlled trial.

All procedures follow CONSORT (Consolidated Standards of Reporting Trials) guidelines and follow four phases: enrollment, intervention allocation, follow-up, and data analysis. The follow-up will occur 3 months after completion of the intervention. The trial has been registered at ClinicalTrials.gov (NCT05640492).

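### The 3-month look-back for prior similar training is no longer than the interval at which the protocol expects MCT-Silver still to work, so previously trained people, most plausibly treated pilot participants, could enter the RCT

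*Protocol article*

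**What the plan says.** Section 2.2.2.2 (Exclusion criteria) lists as item 6 "not having attended a similar training in the last 3 months". Taken literally, this excludes people without recent training. The evident intent is the reverse, to exclude people who attended "similar training in the last 3 months", and the rest of this point uses the intended reading.

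Four other places bear on the length of the window:

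- Section 2.1 (Aim) states the primary hypothesis as a greater reduction in self-reported depression "as measured by the Beck Depression Inventory-II) for MCT-Silver vs. TAU (pre-post; pre-follow-up", so it covers follow-up as well as post-treatment.
- Section 2.2.1 (Study design) fixes the time point: "The follow-up will occur 3 months after completion of the intervention".
- The Discussion paragraph of the abstract repeats the expectation: "It is expected that after 8 weeks of treatment and 3 months later, the experimental group will demonstrate significant reductions in depressive symptoms".
- The Introduction reports from the German RCT against cognitive remediation (CR) that "MCT-Silver yielded significant moderate to large effects compared to CR immediately following the intervention and after 3 months for self-reported depression", with a partial eta squared of 0.075 to 0.135 on the BDI-II.

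On the pilot, section 2.2.4 (Sample size calculation) says "For the pilot study, we will include 32 participants" and that its results will feed the RCT sample size. The end of the Introduction adds that the intervention may be adjusted in the light of the pilot before the team continues to the RCT. No listed criterion mentions pilot participants.

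**The concern.** A washout for earlier exposure to the tested programme should outlast the period over which that programme is expected to act. Here the two are equal. A person who finished MCT-Silver, or its parent programme D-MCT, slightly more than 3 months before screening passes criterion 6 at about the moment when the trial's own hypothesis predicts a detectable benefit.

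Two things are at stake. First, a previously trained person randomised to MCT-Silver repeats the same or closely related manualised content and may gain less from it, which pulls the observed contrast with TAU towards zero. Second, if such people come from the pilot, the RCT would re-use individuals whose data had already helped to set its sample size and shape its intervention, so the two studies would no longer be independent.

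**Working it through.** **1. The two durations.** Look-back: 3 months (section 2.2.2.2). Follow-up at which benefit is predicted: 3 months after the intervention (sections 2.1 and 2.2.1). In weeks, 3 × 365.25 / 12 / 7 = 13.0 for each, a difference of 0.

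**2. Where such an entrant would stand.** Someone whose earlier training ended just over 13.0 weeks before baseline would be about 13.0 + 8 = 21 weeks past it at the post assessment and about 21.0 + 13.0 = 34 weeks past it at follow-up. The protocol makes no prediction for MCT-Silver that far out.

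**3. Who could be exposed.** The abstract says the training has so far been tested only in Germany, so the evident Portuguese source is this team's own pilot. The article does not describe the pilot's arms or schedule. Assuming a 1:1 split, about 32 / 2 = 16 people would be trained. Assuming the pilot follows the RCT schedule, they would clear the window as their 3-month follow-up fell due.

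**4. Do the other design features close the gap?**

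- The MADRS threshold (above 8) removes people with few remaining symptoms but not partial responders. In the cited German trial, group differences appeared on the self-rated BDI-II and not on the Hamilton scale (partial eta squared 0.001 to 0.002). A clinician-rated entry score is therefore not a dependable screen for carry-over on the BDI-II.
- Randomisation balances prior exposure between arms in expectation. It does not restore a gain that a trained person no longer has left to make.
- Baseline BDI-II as a covariate (section 2.2.9) adjusts for the starting score, not for reduced capacity to benefit.
- Previous or current treatment is a planned moderator, but it does not single out metacognitive training.

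**5. Size: illustration only.** The article states no RCT sample size, alpha, power or exposed share, so there is no figure of the plan's to reproduce. Assume two-sided 5%, 80% power, 1:1 allocation and the German effect. Then d = 2 × √(η² / (1 − η²)), n per arm = 2 × (1.96 + 0.84)² / d², and power = Φ(d × √(n/2) − 1.96).

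- η² = 0.075: d = 2 × √(0.075 / 0.925) = 0.57, 49 per arm.
- η² = 0.135: d = 2 × √(0.135 / 0.865) = 0.79, 26 per arm.

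If a share p of entrants is previously trained and gains a fraction r of the usual benefit, the effect becomes d × (1 − p × (1 − r)). Power at the same n is then:

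| p | r | d 0.57, 49 per arm | d 0.79, 26 per arm |
|---|---|---|---|
| 5% | 0.5 | 0.785 | 0.793 |
| 5% | 0 | 0.764 | 0.772 |
| 10% | 0.5 | 0.764 | 0.772 |
| 10% | 0 | 0.718 | 0.727 |
| 20% | 0.5 | 0.718 | 0.727 |
| 20% | 0 | 0.616 | 0.625 |

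With 2 × 49 = 98 randomised, p = 10% means about 10 people, well over half of the assumed 16. If all 16 joined, p would be 16 / 98 = 16%. With 2 × 26 = 52 randomised it would be 16 / 52 = 31%, but only if every one of them was eligible and volunteered. The lower rows of the table are therefore extreme cases.

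**The case against.** The strongest reply is that nothing shows an effect at the time it would matter. The 3-month visit is simply the last measurement. The article is silent on MCT-Silver beyond it and calls the long-term efficacy of D-MCT equivocal. Entrants must also be symptomatic and are measured as change from a new baseline, so residual benefit is largely absorbed there. In TAU, a stable carry-over adds nothing to the change score, and a waning one would widen the contrast. Exposure in Portugal is probably rare, since most people with depression there are said to be treated with medication only. No passage says that pilot participants will be enrolled, and a fuller protocol may settle it.

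Most of this stands, and it limits the claim. A reader might infer that treated people would enter with the effect demonstrably present, that both arms would be diluted alike, or that d of 0.57 to 0.79 measures the distortion. The documents support none of these. Persistence past 3 months is an inference, the clear mechanism is a smaller further gain in the MCT-Silver arm, and those d values describe a past between-group difference.

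What the reply does not remove is that the 3-month window is a stated rule, not a detail left to a longer document. As stated, it lets in prior recipients of the tested programme at the point where the trial predicts continued benefit.

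**Conclusion.** The point holds in a limited form. The look-back equals the interval at which benefit is expected, and nothing listed prevents a previously trained person, including a treated pilot participant, from entering the RCT after it lapses. The consequence is possible dilution, mainly through the MCT-Silver arm, and a loss of independence from the pilot. It is not systematic bias, because allocation is random.

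The size cannot be derived from the documents. The table shows only what would follow from an assumed share, an assumed residual gain and an assumed sample size. At a 5% share the loss from 80% power is about 1 to 4 points. Larger losses need most of the trained pilot group to re-enter or to gain nothing further. A reader might go on to conclude that pilot participants will be enrolled or that the trial will be underpowered; the article says neither. This is a cheap improvement, not a threat to the trial's validity.

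**What to change.** In section 2.2.2.2, exclude anyone who has previously attended MCT-Silver or D-MCT, whenever that was, and state that participants of this study's pilot, in either arm, are not eligible for the RCT. A time-limited window can remain for other group programmes. The inverted wording of item 6 needs its own correction and can be dealt with in the same edit; correcting it alone would leave the window unchanged.

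The cost is one sentence and one screening question, ideally before RCT enrolment starts. The downside is that the 32 pilot participants and a few previously trained patients cannot be enrolled.
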